## Abstract

**Objective:**

To establish the feasibility and effectiveness of a rehabilitation programme using low-cost virtual reality aimed at improving postural control in children with cerebral palsy—spastic hemiplegia. It also aims to compare the effectiveness of this programme under two delivery modalities, telerehabilitation (TR) and face-to-face (FtF).

**Methods:**

This is a registered randomized controlled clinical trial protocol (ACTRN12621000117819). Eighteen sessions of low-cost virtual reality therapy will be provided through both, FtF and TR modalities using a Nintendo Wii balance board. Each programme will last for 6 weeks and will consist of 3 sessions per week of 25 minutes each. Twenty patients diagnosed with cerebral palsy—spastic hemiplegia will be recruited for each group: FtF or TR (n = 40). Participants will be assessed at baseline, by the end of weeks 2, 4, and 6, and at weeks 8 and 10 (post-intervention follow-ups). The primary outcome will be the Center of Pressure sway area (CoP_area_); secondary outcomes will be standard deviation and velocity of the CoP in the mediolateral and anterior-posterior directions; tertiary outcomes will include the Modified-Modified Ashworth Scale for lower limbs, Modified Ashworth Scale for upper limbs, timed up-and-go tests, the timed one-leg standing and 6-minute walk test.

**Results:**

This study provides an assessment of the feasibility and effectiveness of an affordable rehabilitation programme using low-cost virtual reality aimed at improving postural control in children with cerebral palsy.

**Conclusion:**

The designed rehabilitation programme using low-cost virtual reality may improve postural control in children with cerebral palsy—spastic hemiplegia. The TR modality is likely to be as effective as the FtF modality. The TR programme has been designed to overcome access barriers to physiotherapy services for children with cerebral palsy in low-resource settings, remote areas, and in restricted mobility contexts.

## Introduction

Cerebral palsy (CP) is the most common condition treated by therapists in infant neurological units, and it is the most common cause of motor disability in children and adolescents [1, 2], with an increasing prevalence in developing countries [3]. According to the topographical classification, spastic hemiplegia (SHE) is one of the most prevalent types of CP [1, 4]. In SHE, the mobility of one side of the body is more affected, generating poor postural control during standing, leading to impaired performance in daily functional activities [5, 6]. To date, most studies have focused in developing interventions to improve upper-limb function in SHE, for example, virtual reality interventions, which further allow undertaking therapeutic training at home [7–9]. The development of therapeutic interventions aimed at improving postural control, on the other hand, has received less attention [10–12].

Efficient, inexpensive, remotely accessible, and engaging are some of the highlighted characteristics sought after in the development of novel physiotherapy interventions, particularly in children living in low clinical resources/access and remote areas [13–16]. The development of such interventions has been further emphasised since the recent COVID-19 pandemic, which interrupted non-essential rehabilitation services including those focusing on patients with CP and imposed mobility restrictions (lockdowns) [17]. An alternative to meet the aforementioned demands is the use low-cost technological tools and exergames to deliver telerehabilitation (TR) interventions. Additionally, the use of exergames in TR can help improving the quality and quantity of neurorehabilitation in the often-underserved population of children with CP. It is noteworthy, however, that previous studies suggest that a flexible dual-care model that integrates hospital/clinic and home-based TR rehabilitation is more efficacious than TR alone [13]. To date, two studies using TR in children with CP have shown promising results in terms of feasibility and effectiveness compared with standard face-to-face (FtF) interventions, however, these studies have not reported objective outcomes [14, 15].

Low-cost virtual reality exergames are well-accepted by children and adolescents due to their ludic, motivating and engaging features, which facilitate a nearly seamless incorporation into TR [16]. However, high-level evidence of the superiority of TR using low-cost virtual reality in comparison to FtF at clinical facilities interventions is still lacking. It is noteworthy that low-cost virtual reality TR also brings the possibility to standardize rehabilitation interventions, which is a pending task in neurorehabilitation [18]. By 2022, commercially available virtual reality systems cost around $500–1000 USD. Although cheaper options exist, they require to use smartphones, which increases the final cost. For this project, low-cost virtual reality refers to a system valued $100–200 USD, which in middle to high income countries is low [19, 20] in comparison to the out-of-pocket cost for transport to physical rehabilitation facilities. There are no brand-new systems for exergaming within the referred price range, nonetheless, refurbished Wii consoles, for example, can be found for <$200 USD.

This clinical trial protocol aims to establish the feasibility and effectiveness of a rehabilitation programme using low-cost virtual reality to improve postural control in children with CP. It also aims to compare low-cost virtual reality under two delivery modalities, telerehabilitation (TR) and face-to-face (FtF, control group). We hypothesize that a rehabilitation programme using low-cost virtual reality will improve postural control in children with CP and that this programme delivered using TR will be as effective as a FtF modality. The TR programme is designed to expand the coverage of physiotherapy services for children with CP in low-resource settings and in remote areas, but also to provide access to physiotherapy during restricted mobility as in the case of recent COVID-19-related lockdowns.

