### Sample size

Using centre-of-pressure (CoP) sway area (CoP_area_) results from earlier studies [11, 22], to achieve an 80% statistical power with an alpha level of 0.05 and considering a standard deviation of 4.974 cm^2^ (after a 6-weeks intervention), we calculated a required minimum of 20 participants in each group (FtF and TR). This sample size includes a 5% attrition, which yields a total sample size of n = 40. Sample size calculation was performed using GRANMO (Institut Municipal d’investigació Médica, Barcelona, Spain). Once the investigative work has been carried out, the sample size will be verified again, and the estimation error will be adjusted. Feasibility of this study is ensured by our previous work with similar sample size, target population, outcomes, and funding [10].

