### Data analysis

Descriptive statistics will be used to summarize the demographic and clinical characteristics in both intervention groups, and unpaired t-tests and chi-square tests will be used for comparisons. For all outcome measures, the Shapiro–Wilk and Levene tests will be used to measure the normality and homogeneity of the variance, respectively. If the assumptions of normality are met, a t-test will be employed, otherwise we will use Mann–Whitney U test to determine differences between the FtF and TR groups. Also, if the assumptions of normality are fulfilled, we will employ a repeated measures analysis of variance (RM-ANOVA), otherwise will be use Friedman’s test. Post-hoc pairwise comparisons will be used to determine the interventions effect over time for each group (FtF and TR). Cohen´s *d* will be used to report effect sizes for the CoP variables. To allow repeated measures analysis, missing data will be adjusted by 1) replacing with the non-missing average values for each variable/week, and 2) performing multiple imputations. Both methods will be used to make sure that the results were concordant. For all analyses, a *p*-value ≤0.05 will be considered statistically significant. All statistical analyses will be performed using IBM-SPSS 20.0 (SPSS Inc., Armonk, NY, USA).

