## Discussion

The aims of this clinical trial protocol are to establish the feasibility and effectiveness of a low-cost virtual reality to improve postural control in children with CP and to compare two low-cost virtual reality delivery modalities, telerehabilitation (TR) and face-to-face (FtF). We hypothesize that low-cost virtual reality will improve postural control and that both delivery methods will be equally effective. The results of this study will help to support remote access to rehabilitation services and deliver higher, compared to standard, intensity interventions. Further, this trial will support standardization and collaboration in the field of telerehabilitation by incorporating objective measures of postural control to already existing clinical measures.

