### Benefits of remote access to rehabilitation services

We have previously shown that a FtF virtual reality intervention was effective at improving static and dynamic postural control and reducing spasticity in children and adolescents with spastic cerebral palsy [29–32]. Demonstrating that a TR is as efficient as a FtF is crucial to adopt TR as an alternative to expand the coverage and overcome access barriers to rehabilitation services for children with CP in low resources and remote areas. The TR intervention proposed in this protocol is less reliant on clinicians, which can help clinicians to prioritise appointments for those children with greater needs. Further, through direct involvement in the process, TR will empower patients and carers to (self-)guide rehabilitation and participate in selecting most engaging and motivating exercises (exergames) to maintain adherence to treatment. Patients and carers can also benefit from reducing the economic and time burden of travelling to/from clinical facilities to receive physiotherapy treatments [18, 19]. In the recent COVID-19 pandemic context, a TR modality can offer a greatly needed alternative to avoid interruption of the rehabilitation process when mobility restrictions are in place (i.e. lockdowns).

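### The hypothesis is that TR is as effective as FtF, but the only between-group analysis tests for a difference, and no margin, interval rule or target difference is stated

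*Protocol article*

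**What the plan says.** The comparative hypothesis appears in three places. The Introduction expects that "this programme delivered using TR will be as effective as a FtF modality". The Discussion repeats that "both delivery methods will be equally effective". The section on the benefits of remote access gives the reason it matters: "Demonstrating that a TR is as efficient as a FtF is crucial to adopt TR as an alternative".

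Under Data analysis, the two arms are compared by a t-test, or by a Mann-Whitney U test if normality fails, "to determine differences between the FtF and TR groups". The criterion for every analysis is that "a *p*-value ≤0.05 will be considered statistically significant". Repeated-measures ANOVA or Friedman's test, with post-hoc comparisons, covers change over time within each group. Cohen's d is to be reported for the CoP variables, with no rule that links it to a conclusion.

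Under Sample size, 20 children per group, including 5% attrition, are required "to achieve an 80% statistical power with an alpha level of 0.05", "considering a standard deviation of 4.974 cm^2^ (after a 6-weeks intervention"). The paragraph gives no difference to detect, no margin and no hypothesis type.

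**The concern.** A claim that one delivery mode is as effective as another is an equivalence or non-inferiority claim. It is supported when the CI for the difference excludes any disadvantage larger than a stated margin. A test of no difference can reject equality but cannot establish it, because a large p-value arises as readily from too few patients or noisy measurement as from equal effects.

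The hypothesis, the analysis and the sample size therefore do not fit together. The trial's stated use is to justify TR as an alternative to therapist-delivered sessions for children with cerebral palsy. Under the plan as written, a shortfall of TR that is small relative to the trial's precision would most often give a non-significant result, and the plan has no criterion for telling that result from real equality.

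**Working it through.** **Inputs from the protocol.** SD 4.974 cm², power 80%, alpha 0.05, 20 per arm including 5% attrition, 1:1 allocation.

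**Assumptions.** Two-sided testing (the text does not say). The SD is that of the quantity compared, with no baseline adjustment.

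**1. The plan's own figure.** The attrition step is consistent: 20 × 0.95 = 19 evaluable per arm. The 20 itself cannot be reproduced forward because no difference or margin is given, so it has to be solved backwards.

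**2. Standard error of the TR − FtF difference.** SE = SD × √(2/n) = 4.974 × √(2/19) = 1.614 cm².

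**3. Implied detectable difference at 80% power.**
- Normal approximation: (1.960 + 0.842) × 1.614 = 4.52 cm², or 0.91 SD.
- Exact noncentral t, 36 df: 4.65 cm², or 0.93 SD.
- If one-sided 0.05 was meant (normal approximation): 4.01 cm², or 0.81 SD.

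**4. Precision.** 95% CI half-width = t(0.975; 36) × SE = 2.028 × 1.614 = 3.27 cm², about 0.66 SD.

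**5. Chance of a non-significant result when TR is truly worse.** The protocol names no relevant difference, so these true values are illustrative.

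| True difference | Normal approximation | Exact t |
|---|---|---|
| 2.0 cm² | 76% | 77% |
| 2.5 cm² | 66% | 67% |
| 3.0 cm² | 54% | 56% |

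**6. What 19 per arm can support if the arms are truly equal.** Non-inferiority power at one-sided 0.025 is Φ(margin/SE − 1.960). The margins are assumed.

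| Margin | Power with 19 per arm | Evaluable per arm for 80% power |
|---|---|---|
| 2.0 cm² | 24% | 98 |
| 2.5 cm² | 34% | 63 |
| 3.0 cm² | 46% | 44 |
| 4.0 cm² | 70% | 25 |

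Power reaches 80% only at a margin of about 4.52 cm² (normal) or 4.65 cm² (exact t). For two-sided equivalence, two one-sided tests at 0.05 need a margin of about (1.645 + 1.282) × 1.614 = 4.72 cm². Judged by the 95% CI, the figure is (1.960 + 1.282) × 1.614 = 5.23 cm². Both are normal approximations.

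**The case against.** Several points on the other side are fair.

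- **The basis of the sample size is not stated.** A reader might infer that the trial was sized to find a difference. The Sample size section does not say so. Step 3 and step 6 use the same formula, so 19 per arm fits a target difference of about 0.9 SD and a non-inferiority margin of about 0.9 SD equally well. What stands is that neither is given.
- **Nothing says that p > 0.05 will be read as equivalence.** A reader might infer it, and the planned Cohen's d shows that p is not the only output. The abstract's conclusion is also hedged. What stands is narrower: the plan gives no criterion by which its hypothesis could be supported.
- **The comparison is only one aim.** Feasibility and effectiveness of the programme come first, and the repeated-measures analyses address change over time. That limits the reach of this point to the comparative hypothesis, but the protocol itself calls demonstrating that claim crucial.
- **The article is condensed.** A fuller plan may contain an interval rule. This helps only in part: hypothesis, test and sample size are all stated here and do not match, and a margin would normally determine the sample size.
- **The re-check of the sample size.** After the work is done, "the sample size will be verified again, and the estimation error will be adjusted". One might read this as making the precision target depend on the data. The sentence is too vague for that and may mean only that achieved precision will be reported. It does not supply a margin either way.
- **The illustrative differences have no source in the protocol.** It therefore cannot be said that clinically relevant inferiority would usually be missed, because no threshold of relevance is documented.

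**Conclusion.** The point holds as a mismatch between a stated hypothesis and a stated analysis. A difference test at p ≤ 0.05 cannot support equal effectiveness, no other criterion is given, and the 80% power is attached to no difference or margin.

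On the stated SD, with 19 evaluable per arm and two-sided 0.05, the 95% CI half-width is about 3.3 cm² and the implied detectable difference is about 4.5 to 4.65 cm². For assumed true deficits of 2.0 and 2.5 cm², about 77% and 67% of such trials would give a non-significant result. The half-width and detectable difference rest on the assumptions listed in the working; the 77% and 67% also depend on the illustrative deficits. The logical mismatch depends on none of them.

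**What to change.** 1. Under Data analysis, make the between-arm result the TR − FtF difference in CoP area with its 95% CI.
2. State that p > 0.05 will not be taken as evidence that TR is as effective as FtF.
3. Allow a conclusion of equal effectiveness only if the CI lies within a margin, in cm², that is justified and fixed before the data are seen. Whether the claim is one-sided (non-inferiority) or two-sided (equivalence) is for the sponsor to choose, but the hypothesis wording should match it. If no margin can be defended, restate the comparative aim as estimation of the difference.
4. Restate the power sentence as what n = 40 delivers: about 80% power to exclude inferiority larger than about 4.6 cm² if the arms are truly equal (one-sided 0.025, unadjusted), or a 95% CI half-width of about 3.3 cm².

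The cost is wording in the protocol. No extra patients are needed for this route. The price is that the stated power and the conclusion the trial can reach become less favourable.

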## Materials and methods

### Design

This is a double blinded (therapist and assessors), randomized, controlled trial designed following the Standard Protocol Items: Recommendations for Interventional Trials (SPIRIT), (Fig 1) [21].

**Fig 1 pone.0268163.g001:**
[figure not shown]
Flow chart according to the standard protocol items: Recommendations for interventional trials (SPIRIT). Participants, assessments and interventions. Through the two groups of the trial.

The TR interventions does not require a therapist as in the FtF group, where therapist did not know about the participant’s involvement in the trial (therapist blinding). Assessors will not be able to identify the intervention group either. The trial adheres to the Declaration of Helsinki and the Chilean laws of rights and duties of the patient and research in humans. Ethical approval was obtained from the Ethics Committee of the University of Talca (Ref. No. 24–2018). This study was registered with the Australian and New Zealand Clinical Trials Registry (ACTRN12621000117819). Written informed consent will be obtained from parents and participants over 7 years old; verbal assent will be obtained from younger children.

### Study setting

This study will compare the effect of low-cost virtual reality in two distinct settings. The first setting will be clinical (Telerehabilitation Technology Centre and Neurosciences in Human Movement, Universidad de Talca, Chile) and in which low-cost virtual reality will be delivered in a FtF modality (control group) with therapist interacting directly with the patient. The second setting will be a remote facility with no therapist on-site for the delivery of low-cost virtual reality through TR. The default TR setting will be at-home, however, if a participant does not have adequate access to space and/or equipment, TR will be delivered at school, or rehabilitation centre. To note, in the latter cases (school and rehabilitation centre) no therapist will be involved in the TR delivery. All assessments will be conducted at the same facility in which the therapy will be delivered.

### Sample size

Using centre-of-pressure (CoP) sway area (CoP_area_) results from earlier studies [11, 22], to achieve an 80% statistical power with an alpha level of 0.05 and considering a standard deviation of 4.974 cm^2^ (after a 6-weeks intervention), we calculated a required minimum of 20 participants in each group (FtF and TR). This sample size includes a 5% attrition, which yields a total sample size of n = 40. Sample size calculation was performed using GRANMO (Institut Municipal d’investigació Médica, Barcelona, Spain). Once the investigative work has been carried out, the sample size will be verified again, and the estimation error will be adjusted. Feasibility of this study is ensured by our previous work with similar sample size, target population, outcomes, and funding [10].

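### The sample-size paragraph states no target difference or margin, yet commits to an undefined post-trial check of the sample size that is misleading, uncheckable or redundant on its plausible readings

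*Protocol article*

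**What the plan says.** All of this is in the protocol article.

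- **Sample size, inputs.** The calculation is set "to achieve an 80% statistical power with an alpha level of 0.05 and considering a standard deviation of 4.974" cm², an SD described as applying after six weeks of intervention. The result is 20 per group, 40 in total, with 5% attrition included. The inputs are said to come from earlier sway-area results, and the software was GRANMO. No difference, effect size, margin, sidedness or test is given.
- **Sample size, later step.** Once the trial work is finished, "the sample size will be verified again, and the estimation error will be adjusted".
- **Introduction.** The between-arm hypothesis is that "this programme delivered using TR will be as effective as a FtF modality". The Discussion repeats the idea of equal effectiveness.
- **Data analysis.** The arms are compared by a t-test or Mann–Whitney test, and for every analysis a p-"value ≤0.05 will be considered statistically significant".
- **Recruitment.** Screening ends when the calculated sample size has been reached. No extension is described.

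**The concern.** A statement of 80% power means nothing without the difference it refers to, and a later verification needs something to verify against. The article supplies neither, and it still commits to a verification and an adjustment once the data are in. This is more than detail left to a fuller document: the article announces a procedure and leaves its benchmark, its object and its consequence undefined.

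The timing matters because of the hypothesis. The trial hopes to find no difference between telerehabilitation and face-to-face delivery, and it compares them with a difference test. A non-significant p-value is therefore the hoped-for result, and that is where power recomputed from the observed effect misleads most. It will be low whether the arms are truly alike or truly different, and it tells the reader nothing that the p-value has not already told.

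**Working it through.** **Inputs.** From Sample size: SD 4.974 cm², power 80%, alpha 0.05, 20 per group including 5% attrition. Evaluable: 20 × 0.95 = 19 per group. Assumed, because not stated: two-sided, two independent samples.

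**1. Can the stated 20 per group be reproduced?** Not forward, because the difference δ is missing. With n = 2 × (SD × 2.802/δ)², rounded up, then divided by 0.95 and rounded up:

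| Assumed δ (cm²) | n evaluable | n with attrition |
|---|---|---|
| 3 | 44 | 47 |
| 4 | 25 | 27 |
| 4.5 | 20 | 22 |
| 4.6 | 19 | 20 |
| 5 | 16 | 17 |

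Only a δ of about 4.5 to 4.6 comes close to 20. The attrition step itself is consistent: 19/0.95 = 20.

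**2. Back-solving the difference.** δ = SD × √(2/n) × (1.960 + 0.842). With n = 19: 4.974 × 0.3244 × 2.802 = 4.52 cm², or 0.91 SD. The t-based version gives 4.65 cm², or 0.93 SD. Other assumptions give other values: one-sided, 4.01 (t version 4.09); 4.974 read as the SD of a paired change, 4.974 × 2.802/√19 = 3.20 (t version 3.38).

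**3. Reading A: the check uses the observed difference and SD.** Observed power is found by setting the noncentrality of the t distribution (36 df, critical value 2.028) to the observed t:

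| p | observed t | observed power |
|---|---|---|
| 0.05 | 2.03 | 51% |
| 0.30 | 1.05 | 18% |
| 0.50 | 0.68 | 10% |

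Observed power depends on p alone and falls as p rises. Every p above 0.05 gives less than about 51%, so no non-significant result can ever reach 80%.

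**4. Reading B: the check keeps the design difference and updates only the SD.** This is not circular, but the difference is unpublished, so a reader cannot repeat it. It is also unstable. If the true SD is 4.974, the observed pooled SD on 36 df lies between 3.83 and 6.12 in 95% of trials (4.974 × √(χ²/36)). With δ = 4.52 the required n then runs from 12 to 29 per group through sampling error alone.

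**5. Reading C: estimation error means precision.** Expected 95% CI half-width for TR minus FtF: 2.028 × 4.974 × √(2/19) = 3.27 cm². The reported interval will use the observed SD in any case, so a separate adjustment adds nothing.

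**The case against.** The strongest reply is that the sentence is vague but harmless. Alpha is called alpha in the same paragraph, so estimation error more naturally means precision. Data analysis fixes the significance threshold for all analyses, and Recruitment stops at the calculated size. A two-mean calculation at 80% power needs a difference as input, so one was presumably entered even though the condensed article does not print it. The check could reuse that value and would then not be circular.

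Much of this stands. A reader might infer from the word adjusted that the trial's error rate will depend on the data. The documents do not support that: no passage describes a changed threshold or added participants. If the check is only reported, simulated type I error stays at 0.050. Inflation appears only under rules that the article does not contain. Starting from 20 per arm, adding 10 per arm after a non-significant result gives 0.077, adding 20 gives 0.084, and relaxing alpha to 0.10 gives 0.100. Circularity is likewise a property of Reading A, not of the text as such.

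What the reply does not rescue is the step itself. Reading B leaves the reader unable to check it, and Reading C duplicates the confidence interval. Nor does brevity explain it, since the article chose to state the step.

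**Conclusion.** The point holds in a limited form. The paragraph gives power, alpha and SD with no target difference or margin, and it commits to an undefined post-trial verification and adjustment. That step restates the p-value if it uses the observed effect, cannot be checked if it uses the unpublished difference, and is redundant if it concerns precision. It would threaten the 5% error rate only if it led to a new threshold or more participants, and the article does not say that it will.

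The practical size is this. Any non-significant comparison would show observed power below about 51%. If a two-sided two-sample test was used with 19 evaluable per arm, the 80% power applies to a gap of about 4.5 to 4.65 cm², close to one SD, which is a long way from support for equal effectiveness. These figures rest on SD 4.974 and on the assumed test. They are reference values, not the sponsor's design difference. The matter should be corrected, but as written it changes neither the planned test nor the planned sample.

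**What to change.** 1. Delete the sentence on post-trial verification and adjustment. Keep alpha at 0.05, as Data analysis already has it.
2. In Sample size, state the difference, the test and the sidedness actually entered in GRANMO. The back-solved 4.5 to 4.65 cm² can serve to check that entry but should not be written in as the design value, because a one-sided or paired basis would give a different figure.
3. Say that TR versus FtF will be judged by the 95% CI for TR minus FtF, with an expected half-width of about 3.3 cm², and not by a non-significant p-value or by power computed after the fact.
4. Optional: if the SD assumption needs checking, do so by a pre-specified rule on the pooled SD, blind to arm, before enrolment closes and with alpha unchanged.

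Items 1 to 3 cost wording only. The one drawback is that the stated power will look less favourable once its difference stands beside it.
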